## Methods/Design

### Design

This randomised controlled trial has been registered in clinicaltrials.gov (NCT01619930). It will feature four treatment groups and a waiting list control group with delayed treatment: (1) physical exercise without treatment rationale; (2) physical exercise with treatment rationale; (3) BA with treatment rationale; (4) BA without treatment rationale; and (5) a waiting list control group, the participants of which will be randomised evenly to the four treatment groups after a 12-week delay. Participants will be recruited in several cycles over an estimated period of 1 year, with the participants of every cycle being evenly distributed to the five groups. Even distribution of participants to the different cycles will be pursued. After the treatment period of 12 weeks, 50% of each of the four treatment groups will receive a relapse prevention program. All participants will be monitored for 24 months post treatment (Figure 1).

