#### Primary outcome

PHQ-9 [20] is the depression module of the Patient Health Questionnaire (PHQ), designed to score each of the nine DSM-IV criteria for depression as ‘0 (not at all)’ to ‘3 (nearly every day)’, allowing it to be used as both a diagnostic instrument and symptom severity scale. PHQ-9 has been shown to have good internal consistency (Cronbach’s alpha 0.86 to 0.89), good diagnostic validity [34,35] and adequate sensitivity to be used as an outcome measure [36,37]. Participants will complete the PHQ-9 weekly during the treatment period, immediately upon completion of treatment and then monthly during follow-up (24 months).

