### Analysis

The study design will allow for multiple comparisons: the two physical exercise groups (separately and together) will be compared to controls, as will the two BA groups (separately and together). In all other analyses, the groups in question will include those from the control group later randomised to interventions, this to increase the statistical power. The two physical exercise groups will be contrasted with the two BA groups. Further, the physical exercise group with treatment rationale (group 1) will be contrasted with the group without (group 2), and the BA group with treatment rationale (group 3) will be contrasted with the BA group without (group 4). Finally, the four groups receiving relapse prevention will be contrasted with the four groups that do not. At the 12- and 24-month follow-ups, within-group comparisons will be made with previous results.

A number of statistical analyses will be deployed. Treatment outcomes will be examined using mixed effect models, Bonferroni-correcting for multiple comparisons. This method is deemed preferable to uni- and multivariate repeated measures of variance [40], especially since the study has built-in data-loss. The Kaplan-Meier estimator will be used to estimate survival rates during the study period. To find potential predictors of treatment outcomes (including treatment adherence and drop-out), logistic regression analysis on background variables will be performed (see [41]).

Since all questionnaire data will be supplied directly by the participants through the online interface, there is no risk of data loss or data distortion along the way. Data will be stored encrypted and in unidentifiable form (using participant-numbers). Standard missing data analysis will determine if unexpected missing data due to participant drop-out are random or not.

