### Ethics

This study has been approved by the regional Ethical Board. As in any trial, there are a number of ethical concerns, all of which will be adequately addressed. First and foremost, great care will be taken not to include participants too severely depressed or suffering from other disorders better treated elsewhere. Should suspicion arise during the intervention period that an enrolled participant is experiencing a significant decline in health due to the intervention, the supervising clinicians (licensed psychologists, psychotherapists or psychiatrist) may opt to end the participation prematurely and direct the participant to other healthcare services. No adverse side effects of BA or physical exercise are expected, yet side effects will nonetheless be investigated by asking standard treatment side effects questions at the post-treatment measurements, in accordance with the recommendations by Linden [42]. As in all internet interventions, the privacy of the participants is of paramount importance [43]. In this trial, participants will use anonymous participant codes to interact with a secure online interface after a two-stage log-in procedure.

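### Observed data cannot determine whether drop-out is random, and the plan leaves open whether measurement continues when participation is ended for decline on treatment

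*Protocol article*

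**What the plan says.** On missing data, the Analysis section of the protocol article says: "Standard missing data analysis will determine if unexpected missing data due to participant drop-out are random or not". The same section sets the main method: "Treatment outcomes will be examined using mixed effect models, Bonferroni-correcting for multiple comparisons". It adds one analysis that touches drop-out: "To find potential predictors of treatment outcomes (including treatment adherence and drop-out), logistic regression analysis on background variables will be performed".

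The Primary outcome section has the PHQ-9 completed every week of treatment, at the end of treatment, and monthly for 24 months afterwards.

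The Ethics section covers the suspicion, during the intervention period, that "an enrolled participant is experiencing a significant decline in health due to the intervention". The supervising clinicians then "may opt to end the participation prematurely and direct the participant to other healthcare services". Side effects are to be investigated by "asking standard treatment side effects questions at the post-treatment measurements".

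The Design section says: "All participants will be monitored for 24 months post treatment". None of these sections says whether the PHQ-9 or the side-effect questions are still collected once participation has been ended.

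**The concern.** Two things in the text combine.

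First, the missing-data sentence promises a result that no analysis of the collected data can give. The distinction that matters for a likelihood-based mixed model is MAR against MNAR, and it turns on scores nobody has seen. A reader of the trial report could take a non-significant test as support for the model when it provides none.

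Second, the Ethics section creates an exit tied to poor outcome. For the 12 weeks of the controlled comparison, waiting-list participants receive measurements and automated feedback but no intervention, so as worded this exit cannot apply to them. If measurement stops at exit, poor outcomes could go missing from the active side of the control contrast only. The possible bias runs towards treatment. Those removed for a decline attributed to the intervention could also be absent when side effects are asked about, and harms would then be undercounted.

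**Working it through.** **Inputs.** From the protocol article: weekly PHQ-9 during 12 weeks of treatment, nine items scored 0 to 3 (Primary outcome); mixed models (Analysis); the exit provision and the timing of side-effect questions (Ethics); 24 months of monitoring (Design). Not given: any drop-out rate or PHQ-9 SD. The plan has no figure of its own on this point to reproduce. All PHQ-9 values below are assumptions.

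**1. Can a test classify drop-out?** Suppose 10% of an arm leaves. In case A their unseen week-12 scores average what the mixed model predicts from their recorded scores. In case B they average 4 points worse. The recorded data are identical, so every test returns the same answer, yet the true arm means differ by 0.10 × 4 = 0.4 points. The planned logistic regression does not help, because it uses background variables and not the unseen outcome. The Diagnosis section can call its interview gaps completely at random because interview months are randomised. Drop-out has no such randomisation.

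**2. Who can leave by the Ethics route?** The trigger is a suspected decline caused by the intervention. The Control group section gives the waiting list no intervention until after the 12-week delay. During the controlled comparison the route therefore exists only in the four active arms. In later contrasts between active groups it exists on both sides.

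**3. Does measurement continue?** The Ethics section ends participation; the Design section monitors everyone for 24 months. Both can hold only if ending participation means ending the intervention, and the text does not say so.

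**4. What does such an exit do to a mixed model?** One active arm of 200,000 participants was simulated with a baseline and 12 weekly scores. Score at week t = intercept (mean 15, SD 4) + slope × t/12 (mean −3, SD 5) + error (SD 2.5), without truncation at the scale limits. The week-12 mean is 15 − 3 = 12, and the SD is √(4² + 5² + 2.5²) = √47.25 = 6.87. Everyone whose score rises above baseline by a set amount leaves. The week-12 mean is estimated by maximum likelihood for monotone missing data, which is valid under MAR. Negative bias favours treatment.

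| Triggering score | Rise that triggers exit | Missing at week 12 | Bias, likelihood model | Bias, completers only |
|---|---|---|---|---|
| Recorded before exit (MAR) | 8 | 9.1% | 0.0 | −0.59 |
| Recorded before exit (MAR) | 6 | 20.5% | 0.0 | −1.08 |
| Not recorded (MNAR) | 8 | 9.9% | −0.40 | −0.71 |
| Not recorded (MNAR) | 6 | 21.5% | −0.93 | −1.22 |
| Not recorded (MNAR) | 5 | 30.0% | −1.34 | −1.55 |

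In SD units the likelihood bias in the last three rows runs from 0.40/6.87 = 0.06 to 1.34/6.87 = 0.20. In the two MAR rows drop-out depends entirely on recorded scores, so it is plainly not completely at random, yet the model is unbiased. A verdict of random or not random therefore does not tell us whether the model is valid.

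**5. Check by pattern-mixture arithmetic.** Bias = excess missing share in the active arm × delta, where delta is the mean gap between unseen and predicted scores (taken as equal in both arms).
- 5% excess, delta 2: 0.05 × 2 = 0.1 points; at an assumed SD of 5, 0.02 SD.
- 30% excess, delta 5: 0.30 × 5 = 1.5 points; 0.30 SD.
- 1% excess, delta 2 to 5: 0.02 to 0.05 points.
- No excess, or delta 0: no bias.

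**The case against.** The strongest reply is that the design already contains the main safeguard. The PHQ-9 is collected online every week, and a clinician who suspects a decline will often be acting on scores already recorded. In that case the mixed model uses those scores and the simulated bias is 0.0, even with about 21% missing. The exit is also discretionary and the Ethics section expects no adverse effects, so such exits may be few; at 1% the arithmetic gives a negligible shift. This stands as a limit on size. It does not guarantee protection, because the trigger is suspicion and not a recorded rise in PHQ-9.

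Four stronger readings are tempting, and the document does not support them:

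- *That the missing-data test chooses or validates the analysis.* The Analysis section says only that drop-out will be classified. It attaches no consequence to the result.
- *That the control contrast is biased and nothing could reveal it.* Bias is possible, not established. The drop-out regression can show part of the pattern. The article is condensed and the SAP is not at hand, so the absence of a named sensitivity analysis is not an error.
- *That those removed are lost to measurement and never asked about side effects.* That is a natural reading of ended participation, but the Design section promises monitoring of everyone, and the Ethics section does not restrict side-effect questions to people who complete treatment. The matter is unresolved, not settled against the trial.
- *That a particular bias can be quoted.* Any figure rests on assumed drop-out rates and deltas. If drop-out and delta are equal across arms, the bias is zero.

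**Conclusion.** The point holds in a limited form. The missing-data sentence is wrong as stated: observed data can give evidence against MCAR but cannot separate MAR from MNAR, so a non-significant result cannot support the mixed model's assumption. This needs no numerical assumption.

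The Design and Ethics sections are unreconciled on whether measurement continues after participation is ended, and during the 12-week controlled comparison this exit is open only to the active arms. If measurement stops, the PHQ-9 contrast with control could be biased towards treatment where the worsening was not recorded before exit, with little or no bias where it was. The illustrative ranges, about 0.4 to 1.3 points by simulation and 0.1 to 1.5 points by pattern-mixture arithmetic at 5% to 30% excess missing, show what is possible under the stated assumptions. They are not estimates for this trial. Undercounting of harms among those removed is likewise a risk that depends on the same unanswered question. The point should be corrected; it does not undermine the design.

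**What to change.** 1. Replace the sentence on whether drop-out is random. State that the mixed model uses all PHQ-9 scores of all randomised participants in their allocated group, under MAR as an assumption that the data cannot test. Examine departures from MAR with a delta-adjusted tipping-point analysis applied to the active arms: worsen the unseen scores step by step and report the delta at which the conclusion changes.

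2. Reconcile the Design and Ethics sections by stating that ending the intervention early does not end data collection. The online PHQ-9 and the side-effect questions continue unless the participant withdraws consent, and exits are reported by group and reason. The clinical decision to stop is left exactly as it is.

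The cost is revised wording, some reminders to participants who stop early, and one sensitivity analysis.

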### Ethics

This study has been approved by the regional Ethical Board. As in any trial, there are a number of ethical concerns, all of which will be adequately addressed. First and foremost, great care will be taken not to include participants too severely depressed or suffering from other disorders better treated elsewhere. Should suspicion arise during the intervention period that an enrolled participant is experiencing a significant decline in health due to the intervention, the supervising clinicians (licensed psychologists, psychotherapists or psychiatrist) may opt to end the participation prematurely and direct the participant to other healthcare services. No adverse side effects of BA or physical exercise are expected, yet side effects will nonetheless be investigated by asking standard treatment side effects questions at the post-treatment measurements, in accordance with the recommendations by Linden [42]. As in all internet interventions, the privacy of the participants is of paramount importance [43]. In this trial, participants will use anonymous participant codes to interact with a secure online interface after a two-stage log-in procedure.

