The study aims to detect a moderate difference in the primary outcome measure (see section 2.4.3 below) with 80% power and a 5% significance level (Bonferroni-adjusted). In accordance with this, the study will feature 500 participants, with 100 in each treatment group (125 after the control group is dissolved and divided) and a total of 250 (half of each of the four treatment groups) receiving relapse prevention.

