#### Relapse prevention

After the 12 treatment weeks and immediate post-treatment measurements, 50% of each treatment group of each recruitment cycle will be offered a relapse prevention program. The program will be based on and be similar to that used in a previous study [30] on relapse prevention for people suffering residual depressive symptoms after having previously received either psychotherapy or anti-depressant medication. The Internet-administered, therapist-assisted, progressive module-based program featured many of the standard components of cognitive behavioural therapy, including psychoeducation, BA, goal formation and mindfulness exercises.

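### The only side-effect questions the article states are asked before relapse prevention begins, so none is timed to capture unwanted effects of that program

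*Protocol article*

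**What the plan says.** The harms plan is one sentence in the Ethics section of the protocol article. It begins "No adverse side effects of BA or physical exercise are expected" and continues that side effects will be looked into all the same, "by asking standard treatment side effects questions at the post-treatment measurements". Relapse prevention is not mentioned there.

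The Relapse prevention section gives the timing of the third intervention: "After the 12 treatment weeks and immediate post-treatment measurements, 50% of each treatment group of each recruitment cycle will be offered a relapse prevention program". It describes a therapist-assisted online program with standard cognitive behavioural components, mindfulness exercises among them.

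The sample-size paragraph under Screening and participants gives its planned size: "a total of 250 (half of each of the four treatment groups) receiving relapse prevention". The Analysis section plans a comparison of the groups with relapse prevention against those without it.

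**The concern.** The trial evaluates three interventions, but the side-effect sentence covers two, and its time point falls before the third starts. A participant harmed or burdened by the relapse prevention program would meet no side-effect question after that exposure, on the schedule as stated.

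This matters for two reasons. First, the Background says no earlier study has examined whether this type of intervention can be delivered over the Internet, so evidence on it should cover unwanted effects as well as benefit. Second, the Discussion acknowledges that the waiting-list control is gone by follow-up. The relapse prevention comparison still has a concurrent half without the program, so it could separate program-related complaints from background ones. If the questions are not put to both halves after the program, that opportunity is lost, and a report of no side effects would reflect the schedule rather than the program.

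**Working it through.** **1. The planned number.** The article gives "with 100 in each treatment group (125 after the control group is dissolved and divided". The waiting list of 100 is split over four arms: 100 / 4 = 25, and 100 + 25 = 125 per arm. Half of all arms: 4 × 125 × 0.5 = 250. This reproduces the stated figure exactly and leaves 250 in the other half.

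**2. The order of events.** Putting the Ethics and Relapse prevention sections together:

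- 12 weeks of BA or physical exercise;
- post-treatment measurements, with the side-effect questions;
- relapse prevention offered to half of each arm;
- follow-up to 24 months, with no side-effect questions stated.

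**3. How the article treats its other measures.** Follow-up occasions are named for each of these:

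| Measure | Stated occasions in follow-up | Section |
|---|---|---|
| PHQ-9 | monthly | Primary outcome |
| GAD-7 | monthly | Secondary outcomes |
| MINI interview | every third month per person, eight in all | Diagnosis |
| IPAQ, QOLI, EQ-5D, TiC-P | months 12 and 24 | Secondary outcomes |
| Medication changes | months 12 and 24 | Screening and participants |
| Side-effect questions | none stated | Ethics |

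The side-effect questions have a stated occasion, but it is not in follow-up. The issue is therefore a badly placed time point, and not only a missing detail.

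**4. What one repeat would allow.** If n people are asked and none reports a given effect, the upper one-sided 95% limit p solves (1 − p)^n = 0.05, so p = 1 − 0.05^(1/n). With n = 250, p = 1 − 0.05^(1/250) = 0.0119, or about 1.2% (the shortcut 3/250 gives 1.2%). This assumes that all 250 take up the program and answer; with fewer, the limit is wider.

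**5. What the comparison of halves could show.** The documents give no side-effect rates, so those below are assumptions. With 250 per half and a two-sided 5% test of two proportions, the power is:

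| Rate without program | Rate with program | Power |
|---|---|---|
| 5% | 10% | 57% |
| 5% | 12% | 80% |
| 10% | 15% | 39% |
| 10% | 20% | 88% |

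The repeat would serve mainly for description and for fairly large differences. No sample-size figure in the plan changes.

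**The case against.** The strongest reply is that this is a condensed article and the harms sentence is not an assessment schedule. A full protocol could repeat the questions later. The wording is also looser than it first appears: the Ethics section does not say the measurements are the immediate ones, it uses a plural, and the Design section uses the phrase post treatment for the whole 24 months of monitoring. This stands in part. A reader might infer that side effects will never be asked about after relapse prevention, but the article does not say so; it states no later occasion. The narrow reading is still the better one. The Relapse prevention section uses the same plural for the single assessment before the program, and the Abstract separates the post-treatment measurement from the monthly follow-up.

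The second reply is that deterioration will be seen anyway. This also stands in part. A reader might infer that the program yields no harms data at all, and that would be wrong: PHQ-9, GAD-7 and MINI run through follow-up in both halves, and EQ-5D and QOLI are collected at months 12 and 24. But these scales do not ask about unwanted effects of a treatment. The design itself accepts the difference, since PHQ-9 is collected weekly during BA and exercise and side-effect questions are added for those two all the same. The clinicians' option in the Ethics section to end participation is not systematic data collection, and the article does not say whether the period it covers includes relapse prevention.

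Third, two premises are softer than they look. Random selection of the half offered the program is not stated in the Design or Relapse prevention sections; it rests on the Discussion's general claim of a randomised design throughout. And one section speaks of people receiving the program while another speaks of its being offered, so actual recipients may be fewer than 250. Both points stand, and neither alters the timing problem.

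**Conclusion.** The point holds in a limited form. As written, no side-effect questions are timed to capture unwanted effects of relapse prevention, a separately evaluated component offered to about 250 people, and the sentence on side effects names only the other two interventions. Worsening of depression, anxiety, health status and quality of life would still be recorded in both halves.

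The size is that of one missing assessment. With it, a zero count for a given effect would bound its rate at about 1.2%, provided all 250 take up the program and answer; without it, no bound can be given. A reader might want a count of affected people who would go unrecorded, but the documents give no rate from which to derive one. The conclusion rests on reading the post-treatment measurements in the Ethics section as those that the Relapse prevention section places before the program.

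**What to change.** Repeat the side-effect questions at one already scheduled follow-up contact after the program has ended, for example the 12-month battery or the first monthly online contact after program end. The article does not give the program's duration, so the chosen contact must be checked against it. Ask the offered and not-offered halves at the same time point, with the items worded so that people not offered the program can also answer. Report the results by relapse prevention allocation, whether or not the program was taken up. Amend the Ethics section to name all three interventions and both occasions. If a repeat is already intended, one sentence there settles the matter.

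The cost is some rewording of a questionnaire already in use and a few minutes of participant time at a contact that takes place anyway. No additional visit, staff or procedure is needed.

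### Side-effect questions are named only for the post-treatment measurements and are not tied to early exit; if leavers are not asked, side-effect rates may be understated

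*Protocol article*

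**What the plan says.** The Ethics section of the protocol article states that "No adverse side effects of BA or physical exercise are expected", and that they will still be looked for by "asking standard treatment side effects questions at the post-treatment measurements". The Relapse prevention section fixes when that is: the programme is offered "After the 12 treatment weeks and immediate post-treatment measurements". No other time point for side-effect questions is named.

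Just before this, the Ethics section provides for an exit during the intervention period. Where there is suspicion that "an enrolled participant is experiencing a significant decline in health due to the intervention", the supervising clinicians "may opt to end the participation prematurely and direct the participant to other healthcare services". The article attaches no side-effect questions to that exit and does not say that it is recorded or reported as a harm.

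The other data collected during treatment are also specified. The Primary outcome section has the PHQ-9 completed weekly, at the end of treatment and monthly afterwards. The Secondary outcomes section gives the GAD-7 at treatment completion and then monthly. The Design section says that all participants will be monitored for 24 months after treatment.

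**The concern.** The trigger for early exit is itself a suspected harm, and the exit comes before the one time point named for asking about harms. The participants whom the plan would itself identify as possibly harmed are therefore those least certain to be asked. If they are not asked, the answers are missing for a reason related to the outcome. The same applies to drop-outs who stop answering, if side effects contributed to their leaving.

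What is at stake is the trial's harms result, not its efficacy result. The article presents the treatments as candidates for wider use in healthcare and expects no adverse effects. A rate drawn mainly from completers would lean towards that expectation. Under the same conditions, comparisons between arms could mislead where arms lose different proportions of participants.

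**Working it through.** **Sequence in the article**

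1. Weeks 1-12: weekly PHQ-9 and therapist support. Participation may be ended on suspicion of intervention-related decline.
2. After week 12: post-treatment measurements, including the side-effect questions.
3. Months 1-24: monthly follow-up, with no side-effect questions named.

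A participant whose participation is ended in step 1 meets the side-effect questions only if still sent the step 2 questionnaires. The article does not say whether that happens.

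**What other data would show.** The PHQ-9 scores the nine DSM-IV depression criteria, so depressive worsening is visible up to exit. It does not ask about other side effects, such as physical complaints from an exercise programme. The GAD-7, after screening, is next given at treatment completion.

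**Size.** The article gives no harm, drop-out or withdrawal rate, so it has no figure to reproduce. The three inputs below are all assumptions:

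- h = 10%: rate among those asked
- d = 20% or 30%: proportion not asked
- k = 2 or 3: risk in those not asked relative to those asked

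True rate = (1 − d)·h + d·k·h. Relative understatement = 1 − h / true rate. Share of cases missed = d·k / ((1 − d) + d·k).

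| d | k | True rate | Reported among those asked | Relative understatement | Share of cases missed |
|---|---|---|---|---|---|
| 20% | 2 | 0.08 + 0.04 = 12% | 10% | 1 − 10/12 = 17% | 0.4/1.2 = 33% |
| 20% | 3 | 0.08 + 0.06 = 14% | 10% | 1 − 10/14 = 29% | 0.6/1.4 = 43% |
| 30% | 2 | 0.07 + 0.06 = 13% | 10% | 1 − 10/13 = 23% | 0.6/1.3 = 46% |
| 30% | 3 | 0.07 + 0.09 = 16% | 10% | 1 − 10/16 = 38% | 0.9/1.6 = 56% |

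**Limiting cases.** With k = 1 the rate among those asked is unbiased, although 20% or 30% of cases go unseen. With d = 0, where leavers are still asked, nothing is missed.

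**Arms.** With k = 3, an arm with d = 20% and an arm with d = 30% would both report 10%, while the true rates would be 14% and 16%.

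**Denominator.** Dividing by everyone randomised does not repair this, because it counts non-responders as unharmed. With d = 20%, the 10% among those asked becomes 0.80 × 10% = 8%, which is further from the truth.

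**The case against.** A reader might infer that leavers are never asked, and that harms are therefore undercounted by design. The article does not say so. It does not describe the post-treatment questions as the sole assessment, and it does not exclude leavers from them. Stopping treatment is not the same as leaving measurement: the questionnaires are online, and the Design section promises monitoring of all participants. For ordinary drop-outs this objection stands. It is weaker for clinician-ended cases, because the Ethics section ends the participation rather than the treatment, and the monitoring statement does not say that it covers them.

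A second objection is that harm is observed during treatment through the weekly PHQ-9 and therapist contact, so participants withdrawn for decline are known to the team. This stands for depressive worsening before exit. It does not cover other side effects, and being known to the team is not the same as being counted in a reported rate.

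A third is that exit and adverse-event procedures are commonly left to a full protocol, which is not shown. That is fair for the details. The point here, however, rests on a timing that the article does state, beside an exit rule that precedes it.

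Two further readings go too far. The article expects no side effects, but it does not say that it expects to report none. The Analysis section speaks of "unexpected missing data due to participant drop-out" and plans to study predictors of drop-out, but it predicts no rate. Its check of whether such data are missing at random cannot recover side-effect answers that were never collected.

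**Conclusion.** The concern holds as a conditional one. As written, the plan places its one named side-effect assessment after an exit whose trigger is a suspected harm, and it does not connect the two. If those who leave are not asked and carry a higher risk, the reported rate is too low. Both conditions are plausible, and the documents settle neither.

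The size cannot be fixed. Under the assumed inputs the true rate would be 12-16% against 10% reported, a relative understatement of 17-38%. Those figures apply the raised risk to everyone not asked, although many may leave for unrelated reasons. The understatement is zero if leavers have equal risk or are still asked. The primary outcome and the efficacy conclusions are not affected. The change is worth making because it is cheap and removes the doubt.

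**What to change.** - Add the side-effect questions to one or more of the existing weekly online measurements, and keep them at post-treatment.
- Send the same questions once to every participant who stops or whose participation is ended.
- Report by randomised arm the side-effect responses, with the number asked and the number answering.
- Report by randomised arm the number of early endings for decline, counted as harms.

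Do not use all randomised participants as the sole denominator for the questionnaire responses, for the reason shown in the working. Collecting a background rate from the waiting list would be a separate request and is not needed here.

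The cost is a few extra items in the existing interface, a short online exit form and a small burden on participants. The rule for ending participation stays as it is.
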